### Research hypothesis

We hypothesize that RT will be more effective than standard care in improving clinical health status. The main hypothesis is that by applying a supervised RT (EXER-COVID Crossover Study) for 6 weeks, we could reduce the perception of persistent symptoms. We could increase physical performance (V̇O_2_max and/or muscle fitness) through the effects of mechanical and endocrine action, and we could modulate the production of immunological and inflammatory markers due to skeletal muscle contraction, which could contribute to reducing the inflammatory process that is usually established in COVID-19 infection. Exercise training is also expected to be more effective in improving cardiovascular measures of resting blood pressure, arterial stiffness, and heart rate variability as compared to no training. If successful, our trial would provide evidence that exercise training has potential for patients with postdischarge symptoms after COVID-19.

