### Randomization, allocation concealment, and blinding

Eligible participants will be randomly assigned to one of 2 sequence orders with a 1:1 allocation using a computer-generated block randomization schedule (Research Randomizer V.4). Assignment will take place through previously constructed balanced blocks, which will allow equiprobable assignment and ensure that each group has the same number of participants. This allocation mechanism will be carried out until 100 total participants are assigned. The assignment keys will be kept in a confidential file in the Navarrabiomed center and will be opened at the end of the study’s analyses. To ensure masking, an alpha-numerical code will be assigned to each study group. This code will be delivered to the associated researcher and will not be revealed to the investigators in charge of processing the data until the analysis of the coded interventions is completed. Additionally, the researchers from the Navarrabiomed center will be responsible for preparing reports for the participants’ safety committee to verify the progress of the study. Following the conclusion of the baseline examination, the appropriate envelope will be opened by a study researcher, and the participants will be informed about their group allocation. Assessors of outcomes will be blinded to patient data, including allocation at baseline and follow-up. Blinding will be used for all laboratory analyses. Owing to the nature of the study, patients cannot be blinded to the exercise training modality.

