### Procedure

Participants will be randomly assigned (1:1) to one of 2 sequence orders using computer-generated random numbers. All participants will complete both group interventions. Therefore, as participants will act as their own control, this approach will remove any potential differences between subjects and reduce the potential bias when estimating the intervention effect. First, eligible and consenting participants will start with the baseline assessment (T0). Second, participants will be assigned to start 6 weeks of either control group (Sequence 1) or exercise training (Sequence 2), T1 (week 6). Third, full crossover occurred after the 6 weeks, during which participants completed a second 6-week period of the opposite condition (T2, week 12). Outcome assessments will be performed at the end of the immediate intervention and control phase and at the end of the crossover intervention phase (Fig. 1). The general procedure is shown in Fig. 2.

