### Secondary outcomes

#### Long-term COVID manifestations

Data on specific symptoms potentially correlated with long-term COVID-19 will be obtained using a standardized questionnaire administered at enrollment via PROMs [40]. At baseline and at the end of each crossover period, participants will be asked about the presence or absence of symptoms related to long-term COVID-19 and whether each symptom persisted at the time of the visit. More than 1 symptom could be reported that reflects symptoms such as functional limitations and clinical characteristics (i.e., nausea/vomiting, impaired visual acuity or blurry vision, anosmia, dizziness, depression, chills, weakness, musculoskeletal pain, palpitations/tachycardia, change of appetite, frustration, cognitive involvement, anxiety/irritability, dryness, impaired concentration, and headache).

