#### Methods in analysis to handle protocol non-adherence and any statistical methods to handle missing data

The study follows an intention-to-treat principle with the use of baseline observation carried forward imputation, where the baseline value will replace missing data [61]. The final analysis population will be fully described and differences from the enrolled population will be presented. Cases that are lost may remain in the analysis, although they will provide less information and reduce the variance of estimated effects less than cases that are present for all measurement times. Adherence will be the number of group sessions attended/in sessions completed by each participant divided by the total number of sessions available × 100. Retention will be the number of participants who remained in the training program for all 6 weeks divided by the total number of participants × 100. Satisfactory adherence is defined as a minimum of ≥80% adherence to the prescribed RT sessions. Any discrepancies in data analysis between the methods will be resolved by a third-party biostatistician. First, descriptive statistics for the overall sample and between groups will be calculated. Second, a sequence 1–2 crossover analysis will be conducted using *t* tests and/or ANOVA to determine changes in primary and secondary continuous outcomes with individual participants as blocking factors. Categorical outcome measures will be analyzed using a McNemar test for data combined across both periods of the crossover. In addition, the proportions of participants reporting or not reporting long-term COVID-19 symptoms at the end of each period will be compared using a 2-proportion *z* test. If this test yields a statistically significant result, the usual test for differences between the effects of the two treatments should not be applied. By neglecting carryover effects using the procedure of Gaus and Högel [62], we expect enough power for investigation of differences. All analyses will be 2-sided. An *α* value ≤.05 will be considered to indicate statistical significance for the primary analysis.

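### The added 2-proportion z test on symptoms names no comparator; as written it compares week 6 with week 12 in the same participants, so it tests a time trend and not exercise versus control

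*Protocol article*

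**What the plan says.** The analysis rules are in the protocol article's section on non-adherence and missing data, under Statistical procedures. For categorical outcomes the section states: "Categorical outcome measures will be analyzed using a McNemar test for data combined across both periods of the crossover". It then adds a second analysis: "the proportions of participants reporting or not reporting long-term COVID-19 symptoms at the end of each period will be compared using a 2-proportion" z test. The next sentence attaches a consequence: "If this test yields a statistically significant result, the usual test for differences between the effects of the two treatments should not be applied". A remark about neglecting carryover by a cited procedure follows.

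The design facts come from other sections.
- Randomization: participants are "randomly assigned to one of 2 sequence orders with a 1:1 allocation".
- Procedure: Sequence 1 is control then exercise, and Sequence 2 is exercise then control. "All participants will complete both group interventions".
- Long-term COVID manifestations: "At baseline and at the end of each crossover period, participants will be asked about the presence or absence of symptoms". The outcome is therefore binary and is recorded at T0, T1 (week 6) and T2 (week 12).

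The article is not consistent about the weight of symptoms. They appear under Secondary outcomes, and the primary outcome is aerobic capacity. Yet the Objectives section defines the primary objective through perceived persistent symptoms, and the Research hypothesis section gives as its main hypothesis that "we could reduce the perception of persistent symptoms".

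**The concern.** The question for symptoms is whether exercise reduces them relative to standard care. The z-test sentence contrasts only the ends of the two periods. In a balanced two-sequence crossover that contrast estimates a period effect. The 2-proportion z test also takes its standard error from two independent samples, whereas here each participant contributes to both proportions.

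Two consequences follow if the sentence is applied as written. Ordinary recovery between week 6 and week 12 could be reported as a significant symptom result with no exercise effect behind it, and a real exercise effect would be almost invisible to the test. The report would also carry two tests on the same symptom data that can disagree, with no statement of which one prevails. The conditional sentence adds to this: under the literal reading, a plain time trend would be a reason not to apply the treatment test.

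**Working it through.** **Inputs from the article.** Allocation is 1:1, every participant has both conditions, and tests are two-sided. The 0.05 level is stated for the primary analysis and assumed here. The sample-size text gives 84 participants (42 per group), with 100 randomized. That calculation is for V̇O2max. The article gives no power figure for the symptom test, so there is none to reproduce.

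**Assumptions.** The article gives no symptom prevalence or within-person correlation. I use prevalences of 45% to 70%, a within-person correlation (phi) of about 0.4 to 0.7, and no carryover unless stated.

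**1. Literal reading, T1 versus T2.** Let pC and pE be the symptom proportions under control and exercise.
- Expected proportion at T1: (pC + pE)/2, from Sequence 1 on control and Sequence 2 on exercise.
- Expected proportion at T2: (pE + pC)/2, with the roles swapped.
- Difference: 0, whatever the treatment effect. A period shift δ gives a difference of δ.

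Example with pC = 60% and pE = 45%: both visits expect 52.5%.

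Example with a time trend only, 70% at T1 and 55% at T2, n = 84 at each visit: pooled p = 0.625, SE = √(2 × 0.625 × 0.375 / 84) = 0.0747, and 0.15 / 0.0747 = 2.01. This sits almost on the 1.96 limit, so about half of trials reject.

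**2. Size when pairing is ignored.** For the same n people, the true variance of the difference is 2pq(1 − ρ)/n. The z test uses 2pq/n. The actual size is 2[1 − Φ(1.96/√(1 − ρ))]:

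| ρ | actual size at nominal 0.05 |
|---|---|
| 0 | 0.050 |
| 0.2 | 0.028 |
| 0.3 | 0.019 |
| 0.5 | 0.0056 |
| 0.7 | 0.0004 |

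**3. Simulation.** 42 per sequence, 20,000 replicates, latent-normal correlations of 0.6, 0.8 and 0.9. Entries are rejection rates.

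| Scenario | T1 vs T2 z test | Exercise vs control z test, treated as independent | McNemar |
|---|---|---|---|
| No effect, no trend | about 0.03-1.2% | about 0.03-1.2% | about 4-5.5% |
| No effect, 70% to 55% trend | 52-53% | about 0.1-1.1% | about 3.5-4.5% |
| No effect, 70% to 50% trend | 81-88% | about 0.1-1.2% | about 3.4-4% |
| 60% vs 45% effect, no trend | 0.1-1.3% | 50-51% | 72-94% |

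The 50-51% entry can be checked by hand: pooled p = 0.525, SE = √(2 × 0.525 × 0.475 / 84) = 0.0771, and 0.15 / 0.0771 = 1.95, so about half reject. Sequence versus sequence at a single visit has power of 31-32% for the same effect.

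**4. All 100 analysed.** With 50 per sequence, a correlation of about 0.45 and assumed rates of 70% versus 50%, the T1 versus T2 test rejects 0.7% and McNemar 98%. With a 15-point period shift and no effect, the rates are 63% and 4%. Sequence versus sequence at T1 has a size of about 5%.

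**5. With carryover.** Suppose the full 15-point effect persists into the control period of Sequence 2. The paired difference is then (15 + 0)/2 = 7.5 points, and McNemar power at 84 completers falls to about 24-38%. The T1 between-sequence comparison keeps the full 15 points and its power of about 31%.

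**The case against.** **The sentence may mean something else.** It can be read distributively: compare the two groups at T1, then again at T2. The samples are then independent and the z test has valid size. This stands as a possible reading, so a reader who infers that the plan certainly commits an independence error goes further than the text. But the sentence names no groups. This reading would also give up the within-participant comparison for which the crossover was chosen, and only T1 is free of the preceding treatment.

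**It may be a carryover check.** The conditional sentence and the carryover remark point that way, and the cited procedure is not available to settle it. If so, the test was never meant to compare exercise with control. The defect remains in another form, because comparing period 1 with period 2 tests a period effect and not carryover.

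**McNemar is already there.** The z test is an addition, so the treatment contrast for symptoms is not lost through the z test itself. This limits the harm. It does not settle what happens when the two tests disagree.

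**The McNemar advantage depends on no carryover.** This is right. The Procedure section describes no washout, and step 5 of the working shows how far the advantage can shrink. It is a reason to keep the T1 between-sequence estimate in view, not to keep the z test.

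**Conclusion.** The point holds, with limits. As literally written, the z test answers whether symptoms changed between week 6 and week 12, and it uses an independent-samples standard error on paired data. That follows from the design and does not depend on the assumed rates. The rejection rates do depend on assumed prevalences and correlations and, except where stated, on no carryover.

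Three stronger conclusions are tempting and are not supported.
- A reader might infer that no reading yields the crossover contrast. Exercise versus control pooled over periods does estimate that difference. Its fault is too large a standard error, hence lower power.
- A reader might infer that ignoring the pairing inflates false positives. Under positive correlation it does the opposite. The false signals under the literal reading come from the time trend.
- A reader might infer that the trial's main result is at risk. The primary outcome is V̇O2max and symptoms are listed as secondary. The Objectives and Research hypothesis sections give symptoms more weight, and that is why the point still deserves correction.

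**What to change.** Make these changes in one edit of the analysis section.
1. Remove the 2-proportion z test as an inferential test.
2. Remove the sentence that follows it. If only the z test is deleted, the words about a significant result would point back to McNemar, and a significant symptom finding would then block the treatment test.
3. Name the paired exercise-versus-control comparison as the main symptom analysis: McNemar on each participant's end-of-exercise and end-of-control reports, with the paired risk difference and its 95% CI.
4. Report T1 and T2 proportions by sequence, and give the T1 between-sequence difference with its CI as a supportive estimate free of carryover.

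The cost is a few sentences of wording. No extra data, visits or participants are needed. One p-value is lost, and the T1 estimate will be imprecise because it uses each participant only once.

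### The plan bars the treatment test after a significant symptom z test that is not a carryover test, without fixing which comparison triggers the bar or which outcomes it covers

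*Protocol article*

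**What the plan says.** The relevant text is one paragraph of the protocol, under Statistical procedures, in the section on non-adherence and missing data. In order, it sets out:

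- an analysis of continuous outcomes in which each participant forms a block: "a sequence 1–2 crossover analysis will be conducted using *t* tests and/or ANOVA to determine changes in primary and secondary continuous outcomes";
- for categorical outcomes, "Categorical outcome measures will be analyzed using a McNemar test for data combined across both periods of the crossover";
- a further comparison of symptoms, by a z test for two proportions: "the proportions of participants reporting or not reporting long-term COVID-19 symptoms at the end of each period will be compared using a 2-proportion";
- then the conditional rule: "If this test yields a statistically significant result, the usual test for differences between the effects of the two treatments should not be applied";
- then a sentence that opens "By neglecting carryover effects using the procedure of" a cited source and expects enough power as a result;
- two-sided testing, with an alpha "value ≤.05 will be considered to indicate statistical significance for the primary analysis".

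Elsewhere, Primary outcome names the change in VO2max, and long-COVID manifestations are listed under Secondary outcomes. Objectives and Research hypothesis, by contrast, put persistent symptoms first. The Procedure section describes crossover directly after 6 weeks and mentions no washout.

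**The concern.** A rule that withholds the treatment test is normally tied to a carryover test. Here it follows a test of symptom proportions, and symptoms are what the trial hopes exercise will change. If that test compares exercise with control, evidence of symptom benefit becomes the reason not to test for benefit.

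Three things are left open: which groups or periods the z test compares, which outcomes lose their treatment test, and what is done instead. An analyst following the text could drop the treatment analysis, possibly including VO2max, because of a secondary symptom result. The replacement would then be chosen after seeing the data.

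**Working it through.** The plan gives no figure for this rule, so there is none to reproduce.

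**Inputs.** From Sample size: 42 per group (84 evaluable) and 50 per group (100 randomized). From the analysis section: two-sided 0.05. The documents give no symptom prevalences, so those below are assumptions.

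**Reading 1: exercise vs control, sequences compared at the end of period 1.** The statistic is z = (p̂1 − p̂2) / √[p̄(1 − p̄)·2/n]. The chance that it is significant is approximately

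Φ{ (|p1 − p2| − 1.96·√[2p̄(1 − p̄)/n]) / √[(p1(1 − p1) + p2(1 − p2))/n] }.

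Example, 90% vs 70%, n = 42: p̄ = 0.80. The null SE is √(2 × 0.16/42) = 0.0873, and 1.96 × 0.0873 = 0.1711. The alternative SE is √((0.09 + 0.21)/42) = 0.0845. Then (0.20 − 0.1711)/0.0845 = 0.342, and Φ(0.342) = 0.634. Summing the binomial probabilities of all outcomes that reject gives 0.66.

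| Symptomatic, control vs exercise | Formula, n = 42 | Exact, n = 42 | Exact, n = 50 |
|---|---|---|---|
| 90% vs 80% | 0.247 | 0.26 | 0.30 |
| 80% vs 60% | 0.516 | 0.52 (0.53 by simulation) | 0.60 |
| 90% vs 70% | 0.634 | 0.66 | 0.73 |
| 90% vs 60% | 0.902 | 0.92 | 0.95 |

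Each entry is the chance that the treatment test is barred. If the z test pools both periods by condition (100 vs 100), simulation with a latent within-person correlation of 0.5 and no carryover gives about 3% with no effect, 52% at 90% vs 80%, 98% at 90% vs 70% and about 100% at 90% vs 60%.

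**Reading 2: period 1 vs period 2, sequences pooled.** Let pC and pE be the prevalences under control and exercise. Period 1 averages (pC + pE)/2 and period 2 averages (pE + pC)/2, so a pure treatment effect cancels. In simulation (50 per sequence, latent correlation 0.5) the bar falls in about 2 to 3% of trials whatever the effect. With full carryover, period 2 becomes (pE + pE)/2 and the difference is (pC − pE)/2. The bar then falls in about 11%, 35% and 65% of trials for exercise prevalences of 80%, 70% and 60% against 90%. The test also treats repeated measurements on the same people as independent samples.

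**Reading 3: an unstated carryover pre-test.** Assume normal data, 42 per sequence, between-person SD 5, within-person SD 2.5 and no treatment or carryover effect. The pre-test uses each person's sum over periods and the treatment test uses the difference. With equal variances these are independent.

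- *Gate as printed, no fallback:* type I error = 0.95 × 0.05 = 0.0475 with the pre-test at 0.05, and 0.90 × 0.05 = 0.045 with it at 0.10. Simulation gives 4.5 to 4.9%.
- *Gate with a first-period fallback:* the sum and the period-1 value have correlation (2 × 25 + 6.25)/√[(4 × 25 + 2 × 6.25)(25 + 6.25)] = 56.25/59.3 = 0.95. When the pre-test fires at 0.05, the period-1 test falsely rejects about 71% of the time. Type I error is then about 0.0475 + 0.05 × 0.71 = 0.083. Simulations with the pre-test at 0.05 or 0.10 range from about 8 to 9%.

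**The case against.** The best defence is that the sentence is a misplaced fragment of an ordinary two-stage crossover procedure. On that view a carryover pre-test was left out, and the next sentence describes the other branch: if the pre-test is not significant, carryover is neglected and the crossover test proceeds. The cited source is not at hand to settle this. It is plausible, and it means the two sentences need not be in flat contradiction. It does not rescue the text, because no carryover test is described and the rule as printed hangs on the symptom comparison.

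Three stronger inferences should be resisted.

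- *That the main test is cancelled exactly when exercise works.* The text does not fix the comparison. Under period 1 vs period 2 a pure treatment effect does not trigger the bar. Even under exercise vs control it is a probability, and only about 26% for 90% vs 80%. The primary outcome is VO2max, and an effect on VO2max alone would not trigger a symptom test. The bar may have been meant for categorical outcomes only, although the paragraph also covers continuous outcomes and sets no limit.
- *That the plan fails to hold 5%.* The 8 to 9% needs a first-period fallback, which the protocol never states.
- *That any natural recovery triggers the bar.* With 84 to 100 people and the same assumed correlation, a 5-point fall between periods triggers it in 8 to 15% of trials and a 10-point fall in 29 to 52%.

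**Conclusion.** The concern holds as a defect in the printed rule. The treatment test is made conditional on a symptom comparison that is not a carryover test, has no stated groups, has no stated scope and leads to no named alternative.

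If the comparison is exercise vs control, the bar falls in roughly 26% to 92% of trials across assumed differences of 10 to 30 points at 42 per group. If it is period vs period, the rate is about 2 to 3% without carryover or period effects and rises with either. These sizes rest on assumed prevalences and, for the period comparison, an assumed latent correlation of 0.5.

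As printed, the cost is lost power and an open choice of analysis. Inflated type I error arises only if a first-period fallback was intended, and the 8 to 9% rests on the assumed SDs. Whether VO2max is affected cannot be decided from the text, and that uncertainty is itself part of the defect.

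**What to change.** 1. Delete the conditional sentence.
2. Prespecify one treatment analysis for the primary outcome that is carried out whatever any other test shows, for example the planned within-participant crossover model with period and sequence terms.
3. Report any sequence or carryover estimate with its confidence interval, descriptively, and never as a condition for testing. Reword the carryover sentence to match.
4. State which groups the symptom comparison uses. For two-period binary data use a paired, period-adjusted method, such as the Mainland-Gart test or a mixed logistic model with period.

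Replacing the crossover comparison with a first-period analysis is a separate trade-off and is not needed to mend this point. The cost is a few sentences in the analysis section. Visits, data collection and sample size do not change.
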